# The Acute VertEbRal AugmentaTion (AVERT) study: protocol for a randomised controlled, feasibility trial of spinal medial branch nerve block in hospitalised older patients with vertebral fragility fractures

**DOI:** 10.1136/bmjopen-2021-059194

**Published:** 2022-06-12

**Keywords:** pain management, geriatric medicine, bone diseases, spine

## Abstract

**Introduction:**

Vertebral fragility fractures (VFFs) are the most common type of osteoporotic fracture found in older people, resulting in increasing morbidity and excess mortality. These fractures can cause significant pain, requiring admission to hospital. Vertebroplasty (VP) is effective in reducing pain and allowing early mobilisation in hospitalised patients. However, it may be associated with complications such as cement leakage, infection, bleeding at the injection site and fracture of adjacent vertebrae. It is also costly and not readily accessible in many UK hospitals.

A recent retrospective study reported that spinal medial branch nerve block (MBNB), typically used to treat facet arthropathy, had similar efficacy in terms of pain relief compared with VP for the treatment of painful VFF. However, to date, no study has prospectively compared MBNB to VP. We therefore propose a prospective feasibility randomised controlled trial (RCT) to compare the role of MBNB to VP, in hospitalised older patients.

**Method:**

A parallel, two-arm RCT with participants allocated on a 1:1 ratio to either standard care-VP or MBNB in hospitalised patients aged over 70 with acute osteoporotic vertebral fractures. Follow-up will be at weeks 1, 4 and 8 post intervention. The primary objective is to determine the feasibility and design of a future trial, including specific outcomes of recruitment, adherence to randomisation and safety. Embedded within the trial will be a health economic evaluation to understand resource utilisation and implications of the intervention and a qualitative study of the experiences and insights of trial participants and clinicians. Secondary outcomes will include pain scores, analgesia requirements, resource use and quality of life data.

**Ethics and dissemination:**

Ethical approval was granted by the Yorkshire & the Humber Research Ethics Committee (*reference 21/YH/0065*). AVERT (Acute VertEbRal AugmentaTion) has received approval by the Health Research Authority (*reference IRAS 293210*) and is sponsored by Nottingham University Hospitals NHS Trust (*reference 21HC001*). Recruitment is ongoing. Results will be presented at relevant conferences and submitted to appropriate journals for publication on completion.

**Trial registration number:**

ISRCTN18334053.

Strengths and limitations of this studyThe two interventions are proven, safe, surgical interventions, already used in existing healthcare practice and adverse events from both interventions are already well documented.The descriptive analysis on effectiveness of outcome measures will inform hypothesis testing in a future definitive trial, including levels of variability required to determine power.It will determine the feasibility of collecting economic measures, including detailed resource use and quality of life data within the two arms, which will aid the design of a comprehensive economic evaluation in a future definitive trial.The nested semistructured qualitative interviews will provide valuable data to inform future trial acceptability for participants and the healthcare professionals involved in their clinical care.

## Introduction

Vertebral fragility fractures (VFFs) are the most common osteoporotic fracture, leading to both acute and chronic back pain, substantial spinal deformity, functional disability, decreased quality of life and increased mortality.^1 2^ The presence of one VFF increases the risk of a new VFF fivefold, and up to 12-fold in the presence of two or more VFFs.^3 4^ These fractures frequently occur with very little trauma from day-to-day activities, such as bending forward, twisting, lifting light objects and sitting from a standing position onto a low chair.^5^

Patients with VFF may have mild to moderate symptoms; however, a significant proportion require hospitalisation due to disabling pain.^6^ The incidence ranges from 10 to 20 per 10 000/year, rising to 50 per 10 000/year in those aged 80 years and over.^7^ Hospitalised patients with VFF tend to be older, frail with coexisting comorbidities and have cognitive impairment. These patients have longer hospital stay and higher mortality.^7 8^ Conservative (non-surgical) treatment for these patients consists of bed-rest, analgesia and, controversially, thoracolumbar bracing.^9^ These are poorly tolerated, and immobilisation leads to muscle wasting, impaired rehabilitation, further bone loss and medical complications such as chest infections, deep venous thrombosis and pulmonary embolism.^10^ Potent morphine-based analgesia leads to nausea, constipation and particularly in those with cognitive impairment and delirium.^11^ Moreover, one in five patients is readmitted within 30 days.^12^

Vertebroplasty (VP) is a minimally invasive, image-guided key-hole procedure that involves injection of radio-opaque bone cement into the fractured vertebral body, in an effort to provide pain relief and stability.^13^ Recent guidelines recommend VP as the first-line treatment for VFF, given its efficacy, cost and minimally invasive nature compared with balloon kyphoplasty (BKP), with BKP reserved for more traumatic fractures in younger people.^14^ Although a Cochrane review concluded that VP had no important benefits,^15^ the limitations of the review were recognised.^16 17^ VP performed within 3 weeks of fracture in older hospitalised patients with severe pain has been recommended,^18 19^ demonstrating a reduction in pain, pain-related disability and hospital length of stay compared with conservative medical treatment.^12 20–22^ A reduction in hospital and long-term mortality has also been reported when compared with conservative treatment.^23–26^

With ageing demographics, we anticipate an increasing demand for VP in hospitalised patients nationally. From our local audit data, 81 patients had VP in Nottingham last year. This amounted to a cost of £650 000, with a single level VP costing £4500. The literature reports complications (range 2.2%–3.9%) related to VP, which includes cement leakage, infection, bleeding at the injection site, fracture of the ribs, posterior elements or pedicle.^26^

Recent studies have shown that steroid injections at the facet joint to block the medical branches from the dorsal rami spinal nerve roots—medial branch nerve block (MBNB)—may be effective in managing pain in patients with VFF.^27^ A retrospective study demonstrated that MBNB had similar efficacy in terms of pain relief and radiological changes after 2 years of follow-up^28^; however, its application in older hospitalised patients needs to be explored. We hypothesise that MBNB will be as effective clinically and cost-effective compared with VP, will be more readily accessible via anaesthetic and interventional radiology service, and will eliminate the risks of adjacent vertebral fracture and cement leakage associated with VP.

## Methods and analysis

### Aims

The ultimate aim of the feasibility trial is to prepare the foundations to design and conduct a multicentre, randomised controlled trial (RCT) of hospitalised older people with painful VFF in order to evaluate the clinical and cost-effectiveness of MBNB compared with routine surgical treatment.

### Objectives

The feasibility of conducting a definitive RCT will be determined by considering the following objectives:

Determine the number of patients who meet the eligibility criteria in addition to the recruitment (including willingness to be randomised) and retention rates of those eligible patients.Test several outcome measures for assessment of mobility, pain and quality of life, for their potential use as a primary outcome measure.Calculate means and SD for the quantitative measures to allow hypothesis testing and development of the analysis plan for a future definitive trial.Evaluate ease of access and availability of information from primary and secondary care databases to determine the most efficient way of measuring patient level healthcare costs.Use of a qualitative nested interview study to assess participants’ and clinicians’ views on trial acceptability, trial processes and define the ‘non-inferiority’ margin to inform the design and conduct of a future definitive trial.

### Study design

The study design is a parallel, two-arm randomised controlled feasibility trial with participants individually randomised on a 1:1 ratio to continue with their planned surgical care-VP or MBNB treatment. Embedded within the feasibility study will be a health economic analysis to understand resource utilisation and implications of the intervention and a qualitative study which will focus on the experiences of participants and clinicians involved in the study, their insights and recommendations for improving trial acceptability and processes.

### Participants

This is single site study (Queens Medical Centre, Nottingham University Hospitals NHS trust) with a catchment population of 800 000. Participants presenting with acute painful VFF and awaiting spinal surgery will be approached for recruitment into the study.

The inclusion and exclusion criteria are as follows:

#### Inclusion criteria

Patients aged 70 years and over admitted to hospital.Ambulatory prior to injury.<6 weeks from date of injury.Numeric Rating Scale (NRS) pain score 7 or more on standing and not responding to analgesia.MRI confirmed oedema at the site of fracture.

#### Exclusion criteria

Debilitating chronic back pain not relieved despite opiate use.Substantial fracture retropulsion; acute infection or spinal malignancy.Three or more acute vertebral fractures.Receiving palliative care.Spinal deformity which contraindicates VP.

### Study procedures

#### Recruitment

Patients who fulfil the eligibility criteria will be invited to participate. Those who indicate an interest will be introduced to the research team and details of the study will be explained: a patient information sheet (PIS) will be provided. Patients will have 24 hours to consider participation before providing informed consent. Consent (online supplemental file) will be obtained in accordance with Good Clinical Practice guidance and will include consent for potential inclusion in the qualitative interview study. Figure 1 illustrates the process of obtaining consent for the study.

10.1136/bmjopen-2021-059194.supp1Supplementary data

**Figure 1 F1:**
[figure not shown]
Flowchart illustrating consent process for the avert trial. AMT, Abbreviated Mental Test; PC, personal consultee.

An Abbreviated Mental Test (AMT) on admission for potential participants will be used as a screening tool for capacity assessment. A patient is deemed to have capacity if their AMT is >7/10 at either point of assessment. If AMT is documented as <7/10, then it will be repeated by the research team at the time of screening, and prompt a capacity assessment in relation to research.

For potential participants who are unable to provide consent, relatives or carers will be approached in the capacity of the participants’ personal consultee.

Patients who decline to take part, or consultees who decline the patient’s participation in the study, will be asked if they would be willing to share their reasons. The information will be valuable for us to improve future trial design and acceptability. However, there will be no requirement to do so and it will not affect the care that their relative/friend receives in hospital if they decline to share this information. The findings will be tabulated into the final results.

### Randomisation

Participants will be randomly allocated to routine care VP or MBNB. Allocation (block randomisation) will be in a 1:1 ratio via a secure web-based system (RedCap Cloud). VP and MBNB will be undertaken within 72 hours of randomisation where possible. Participants and their General Practitioners (GPs) will be notified of their allocated arm in the study and a record of randomisation will be made in the participant’s medical notes.

Due to the nature of the study, it will not be possible to blind the participant or staff to VP surgery or MBNB.

### Intervention

#### Intervention group

This will be performed by a consultant anaesthetist or an interventional radiologist trained in MBNB.

Bilateral MBNB will be performed targeting facet joints above and below the vertebral fracture. Fluoroscopy will be used to assess the optimal position of the needle. A mixture of 0.5% bupivacaine with 40 mg depomedrone will be used. Each medial branch will be blocked with 1–1.5 mL solution.

### Standard care group

#### Vertebroplasty

This will be performed by an interventional radiologist or spinal surgeon under general anaesthesia or conscious sedation using fluoroscopy. The approach will be bipedicular or unipedicular, aiming the placement of the Jamshidi needle (8–12 G in size) at the centre of the vertebral body. A bony biopsy will always precede the injection of the polymethylmethacrylate bone cement. Approximately, a volume of 2–5 mL of the cement will be injected in the vertebral body according to the level and the morphology of the fracture, trying to minimise any leakage.

Usual postoperative care and monitoring will follow after the surgery. Participants will be encouraged to mobilise as pain allows and be prescribed analgesia as required.

### Outcomes

#### Feasibility study outcomes

Number of eligible patients.Rate of participant recruitment and randomisation.Reasons why participants are not recruited or randomised.Rate of participant adherence to randomisation (cross-over) and retention.Completion of study rates and reasons for non-completion.Completeness of data.SD and effect size of potential outcomes for subsequent definitive trial.Time from randomisation to delivery of the intervention.

#### Assessment of outcome measures used in feasibility study for its potential use in a future definitive trial

Functional disability as measured by the 24-point Roland Morris Disability Questionnaire (RMDQ)^29^ (this is the most commonly used outcome measure in previous studies).Pain as measured by the 0–10 Numeric Pain Rating Scale (NRS-11).^30^Quality of Life as measured by the EuroQol (EQ5D-5L) and where appropriate, proxy EQ5D-5L.^31^Activities of daily living as measured by the Nottingham Extended Activities of Daily Living (NEADL) scale.^32^Abbreviated Mental Test (AMT) for cognition assessment.^33^Montreal Cognitive Assessment for cognition assessment.^34^Charlson Comorbidity Index as a predictive tool for 1-year mortality.^35^Clinical Frailty Scale (CFS)—frailty assessment.^36^Sociodemography data including age, sex, socioeconomic status.Record of pain medication use (using the opioid dose equivalence table).

### Analgesia requirement

Analgesia requirement will be recorded as follows: each medication will be classified as a strong opioid (including oxycodone, morphine, fentanyl, pethidine, hydromorphone, buprenorphine and tramadol), mild opioid (including medications containing codeine or dextropropoxyphene) or non-opioid medication (including paracetamol and non-steroidal anti-inflammatory drugs). The participant will be given a score of 0, 1 or 2 in each of these three categories depending on the number of concurrent different medications being taken within each category. Opioid medication will also include a calculation of the oral Morphine Equivalent Daily Dose using the Opioid Dose Equivalence score.^37^

### Follow-up

Participant flow through the study is summarised in figure 2. Follow-up timings will be counted from the time of intervention. Participants will be followed up face to face at week 1 (±3 days) (while in hospital), week 4 (±7 days, telephone interviews) and week 8 (±7 days, telephone interviews).

**Figure 2 F2:**
[figure not shown]
Participant flow through the trial including the timings of data collection.

Follow-up outcome measures will include the following:

Participant still living (established by the hospital’s NHS spine portal enquiry).Hospital length-of-stay (ascertained by the hospital electronic database, supplemented by review of medical notes by a different member of staff to maintain blinding, if necessary).Unplanned hospital readmission within 28 and 91 days post discharge (ascertained by the hospital electronic database, supplemented by review of medical notes if necessary).Health economics/resource utilisation (patient and NHS costs).Time from randomisation to delivery of the intervention.Quality of life measures using RMDQ,^29^EQ-5D-5L.^31^NEADL.^32^NRS.^30^

#### Qualitative assessments

The study will be complemented by a nested semistructured interview to provide essential insights into the feasibility, design and conduct of a definitive trial. This will focus on the experiences of participants (n=10) and clinicians (n=5) in the study, their insights and their recommendations for improving trial acceptability and processes.

A range of participants with different characteristics which we believe might lead them to have a different opinion or experience will be invited for the interview. For example, participants of both genders; participants from both arms of the study, a spectrum of participants on the clinical frailty scale; some patients who may have particular communication needs (eg, deafness, English as a second language speakers). Personal consultees of participants will also be invited to participate in the interview. Similarly, we wish to explore clinical staffs’ thoughts about participant recruitment (eligibility and randomisation), an acceptable non-inferiority margin, as well as reflect on the process of integrating the research with the clinical service. Clinical staff will be identified by the study lead, who will distribute an invitation letter/email and information sheet to eligible staff. All clinicians will be provided with a participant information leaflet, and asked to give written, informed consent, using a dedicated clinician interview consent form.

All interviews will be audio recorded, transcribed in full and anonymised using a professional transcription service.

### Data analysis

A statistical analysis plan will be finalised and approved prior to database lock and commencement of data analysis. Feasibility outcomes will be summarised using appropriate descriptive statistics; mean (95% CI) for continuous and frequency (%) for categorical. Completeness and descriptive summaries of outcome data at each follow-up time point will be presented. Descriptive summaries of NHS costs (using standard unit costs) data at each follow-up time point will be presented.

### Economic evaluation

In addition, at week 8, to inform the definitive economic analysis, we will assess resource use between VP and MBNB treatments; the ease of access to information about resource use from routine database systems; and the feasibility of collecting such data.

Surgical VP and MBNB treatment resource use will be collected from the medical notes and through discussions with participants by the research staff. The cost associated with the surgery will be based on the recorded resource use for the surgery (eg, consumables, equipment, grade and number of nursing staff present during the operation). Further health resource information will be extracted from the hospital electronic system (NotIS) and the GP electronic systems by the research assistant. This will include any outpatient appointment, outpatient procedures, emergency department visits, inpatient admissions related to the study or GP visits captured at baseline, week 4 and week 8.

The unit costs of health resources will be based on national tariffs such as the Unit Costs of Health and Social Care for primary care resources, NHS Reference Costs for secondary care resources and the BNF for prescriptions. These tariffs will be estimated at 2021 prices. We will also use national databases such as the NHS Healthcare Resource Group (HRG) Tariff,^41^ the Personal Social Services Research Unit (PSSRU) Costs of Health,^42^ the Office of National Statistics (ONS) Bulletin Annual Survey of Hours and Earnings^43^ and NHS Reference Costs (https://www.gov.uk/government/collections/nhs-reference-costs). Any unit cost that is not available will be estimated in consultation with the hospital finance department.

### Health economic analysis

We will rehearse the cost-effective analysis to inform the study hypothesis and the analysis plan for the definitive trial. The within-trial economic evaluation will determine the cost and outcome of VP and MBNB treatment from a NHS perspective. The evaluation will follow the reference case guidance for technology appraisals as set out by the National Institute for Health and Care Excellence (NICE).^44^ Effectiveness will be captured using quality-adjusted life-years (QALYs) as assessed by the EQ-5D-5L^31^ at 8 weeks. The primary health economic outcome of the evaluation will be the incremental cost per additional QALY gained from surgical VP and MBNB. To control for the impact of uncertainty, one-way and two-way sensitivity analyses will be performed on (but not exclusively) age, gender and baseline scores. The impact of parameter uncertainty will also be addressed using a probabilistic sensitivity analysis, allowing the calculation of 95% CIs for the incremental cost-effectiveness ratio and cost-effectiveness acceptability curves.

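### The primary economic outcome is an ICER with a 95% CI, but the trial's own hypothesis puts the QALY difference near zero, where that interval is unbounded or uninterpretable

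*Protocol article*

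**What the plan says.** All the economic commitments are in the protocol article's Health economic analysis section. Its stated purpose is preparatory: "We will rehearse the cost-effective analysis to inform the study hypothesis and the analysis plan for the definitive trial". The measure of effect is the QALY: "Effectiveness will be captured using quality-adjusted life-years (QALYs) as assessed by the EQ-5D-5L", at 8 weeks. The headline quantity is a ratio: "The primary health economic outcome of the evaluation will be the incremental cost per additional QALY gained from surgical VP and MBNB". Uncertainty is handled in two ways. First, "one-way and two-way sensitivity analyses will be performed on (but not exclusively) age, gender and baseline scores". Second, a probabilistic sensitivity analysis is planned, "allowing the calculation of 95% CIs for the incremental cost-effectiveness ratio and cost-effectiveness acceptability curves".

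The expected effect is set out in the Introduction: "We hypothesise that MBNB will be as effective clinically and cost-effective compared with VP". The Objectives and Qualitative assessments sections both look ahead to a non-inferiority margin, which fits an expectation of little or no difference in effect. The article gives no QALY difference, no EQ-5D-5L or cost SD, and no cost for MBNB.

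**The concern.** An ICER divides the cost difference by the QALY difference. It behaves well only when the denominator is clearly away from zero. Here the trial expects that denominator to be about zero, over a horizon so short that few QALYs can accrue, and with few participants.

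This is more than low precision. When the QALY difference can take either sign, a negative ratio may mean that MBNB is cheaper and better, or that it is dearer and worse. Where MBNB is cheaper and slightly less effective, a larger ratio (more saved per QALY given up) favours it; where it is dearer and more effective, a smaller ratio does. An interval that ranks all these values on one line has no coherent meaning. More participants do not cure this if the true difference is near zero.

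There is a second, smaller point. Age, gender and baseline scores are characteristics of patients, not uncertain inputs such as unit costs. Varying them one or two at a time does not remove a chance baseline imbalance between arms from the estimated QALY difference.

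At stake are the interpretability of the primary economic output and the method offered to the definitive trial's analysis plan.

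**Working it through.** **Inputs from the protocol article.** The horizon is 8 weeks (Follow-up; Health economic analysis). Allocation is "participants individually randomised on a 1:1 ratio" (Study design). The Sample size calculation section gives 30 recruited and 28 completing. Its chain gives 50 × 0.8 × 0.7 = 28 recruited and 30 × 0.9 = 27 completing, close enough to use 28, or 14 per arm.

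**Assumptions, not in the document.** SD of EQ-5D-5L utility at a visit: 0.15 to 0.30. Normal sampling distributions. Other assumed values are marked where used.

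**1. Most QALYs one person can accrue.** 8/52 = 0.154 (0.153 as 56/365.25 years).

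**2. Standard error of the QALY difference.** SE = SD × k × (8/52) × √(2/14), where k is the ratio of the SD of a person's time-averaged utility to the visit SD.
- Utility constant within person: k = 1.
- Correlation 0.5 between all visits, trapezoid rule over baseline and weeks 1, 4 and 8: the weights are 0.0625, 0.25, 0.4375 and 0.25, with sum of squares 0.320. Then k = √(0.320 + 0.5 × 0.680) = 0.81.

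| Utility SD | SE, k = 1 | SE, k = 0.81 |
|---|---|---|
| 0.15 | 0.0087 | 0.0071 |
| 0.30 | 0.0174 | 0.0142 |

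**3. Probability of a negative denominator.** P = Φ(−Δ/SE), for draws centred on the true difference Δ.
- Δ = 0: 50%, whatever the SD.
- Δ = 0.01 QALY (assumed): 13% to 28% with k = 1 and 8% to 24% with k = 0.81, so 8% to 28% overall.

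**4. Is the ICER interval bounded?** The Fieller 95% set for a ratio is a bounded interval only if the 95% CI for the denominator excludes zero.
- Δ = 0: that CI includes zero in 95% of trials.
- Mean utility difference of 0.05 (Δ = 0.05 × 8/52 = 0.008), k = 1: it includes zero in 86% to 93% of trials.

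**5. Ratio and net benefit from the same draws.** Illustrative assumptions: time-averaged utility SD 0.25, Δ = 0, MBNB cheaper by £2500, cost SD £4000, independent costs and QALYs, and £20,000 per QALY.
- ICER: in 400,000 simulated draws the central 95% ran from about −£2.8m to +£2.8m per QALY.
- Net benefit: its SE is √[(20,000 × 0.01454)² + (4000 × √(2/14))²] = √(291² + 1512²) = £1540. The interval is £2500 ± 1.96 × £1540, about −£518 to £5518 (simulation: −£515 to £5508). The probability of being cost-effective is about 0.95.

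At the same utility SD, with Δ of 0 or 0.008, cost differences of £1000 to £4000 and cost SDs of £2000 to £4000, the ICER limits lay between about ±£1m and ±£4.5m.

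**6. Chance baseline imbalance.** The SE of the baseline utility difference is SD × √(2/14), which is 0.076 to 0.113 for SDs of 0.20 to 0.30. With an assumed carry-over slope of 0.5, one SE corresponds to 0.5 × 0.076 × 0.154 = 0.006 up to 0.5 × 0.113 × 0.154 = 0.009 QALY.

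**The case against.** The strongest reply is that this is one output of a rehearsal in a feasibility trial. No progression decision depends on it, and a rehearsal may itself expose the instability. That limits the consequence. It does not justify the choice, because the stated purpose of the rehearsal is to inform the definitive analysis plan.

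A reader might infer more than the text supports, in four ways.
- **That the whole economic analysis is uninterpretable.** It is not. Acceptability curves, planned in the same sentence as the ICER interval, stay well defined when the QALY difference crosses zero. The Data analysis section also plans descriptive cost summaries.
- **That sensitivity analyses replace baseline adjustment.** The article does not say so. The list is open-ended, adjustment is neither planned nor excluded, and a statistical analysis plan is promised. Only the narrower point stands: analyses of this kind do not correct chance imbalance.
- **That a bootstrap percentile interval is planned.** The article names a probabilistic sensitivity analysis and no interval method. The percentile figures above are illustrative, and the Fieller argument does not depend on them.
- **That MBNB is hypothesised to be cheaper.** The article calls VP costly and gives £4500 for a single level, but gives no MBNB cost. The concern needs only similar effectiveness.

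It is also fair to say that the magnitudes rest on assumed inputs, and that taking utility as constant within person overstates the standard error if visits correlate less than perfectly. Allowing for a correlation of 0.5 lowers the figures but not the conclusion.

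**Conclusion.** The concern holds for the ICER and its 95% CI. Under the hypothesis of similar effectiveness, over 8 weeks and with about 28 completers, the QALY difference has a standard error of about 0.007 to 0.017 around an expected value near zero. The interval for the ratio would then usually be unbounded or without coherent meaning. This follows from an analysis that the article states, not from a detail it leaves out.

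The size depends on the assumed utility SD (0.15 to 0.30), the within-person correlation (0.5 to 1) and, away from zero, the assumed 0.01 QALY gain. At zero true difference, the 50% of draws with a negative denominator depends on neither the SD nor the correlation. The baseline point is secondary: a one-SE imbalance is worth about 0.006 to 0.009 QALY under an assumed slope of 0.5, and the article gives no expected effect to compare it with.

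The effect is confined to this output and to the method passed on to the definitive trial.

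**What to change.** In the Health economic analysis section or the statistical analysis plan:
- Make incremental net monetary benefit, at stated willingness-to-pay values, the primary economic outcome, with a 95% CI.
- Report incremental cost and incremental QALYs separately, each with a 95% CI, together with the cost-effectiveness plane and the acceptability curve already planned.
- Give the ICER as a point estimate only when it is interpretable, and without a CI.
- Estimate the QALY difference with adjustment for baseline EQ-5D-5L. The reference to baseline scores implies that it is collected, although the figure with the data collection schedule is not shown here.
- Use one-way and two-way sensitivity analyses for uncertain inputs such as unit costs.

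The cost is a change of analysis wording, with no new data beyond what is planned. The downside is that the ICER becomes less prominent. Separate cost and QALY intervals with the plane and curve would already remove most of the problem; net benefit adds a single summary whose interval stays valid whatever the sign of the QALY difference.
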